### Blinding

Baseline measurements, except for activity monitoring, are done before randomization. Assessments after the interventional period are done both blinded (insulin sensitivity, blood analyses, reproduction-related hormones, clinical data collected by the hospital during fertility treatment) and non-blinded (peak oxygen uptake, flow-mediated dilatation assessments). However, the analysis of the flow-mediated dilatation will be done blinded.

## Discussion

Lifestyle interventions, including regular exercise, healthful diet, and weight loss, are recommended to improve fertility in overweight and obese women [26]. At present, there are no evidenced-based guidelines on exercise training programs to improve fertility. We also need more knowledge about the underlying mechanisms for improvements in fertility after a period of exercise training. We have presented the rationale and design of a randomized controlled trial for investigating the effect of regular HIT in subfertile overweight/obese women. As insulin resistance and visceral fat deposition are thought to be central mechanisms contributing to decreased fertility in overweight/obese women [6, 27], we hypothesize that an intervention program designed to improve insulin sensitivity and reduce visceral fat will improve the success rate after assisted fertilization. We argue that this study will contribute important knowledge for further recommendations regarding lifestyle interventions in obesity-associated female subfertility.

To our knowledge, this is the first study of HIT as an approach to increase pregnancy rate among overweight and obese women referred to assisted fertilization. If successful, this study will bring new knowledge on preferred procedures to increase fertility rates in this population and offer guidance to clinicians treating these women.

### Trial status and change in study protocol after trial initiation

We are recruiting participants for the FertilEX study. As of March 2016, we have included 16 women in the study. We made a change to the study protocol on 16 February 2016, and from this time point on, the women allocated to the control group no longer wait for 10 weeks before the assisted fertilization treatment starts. This was done because we experienced that several women would not like to participate in the study as they felt that their treatment would be delayed. This study change therefore implies there will be no assessments after 10 weeks for the women in the control group. Also, as of February 2016, we started to include patients from a second fertility center, named Spiren Fertility Clinic, in Trondheim, Norway. This change was made to increase the recruitment to the study.

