**Discussion:**

The results of this trial will provide knowledge about the effects of high-intensity exercise before assisted fertilization in subfertile overweight/obese women. If the intervention leads to beneficial effects on outcome measures, such programs should be considered as part of regular fertility care procedures for this population of women.

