## Background

Obesity prevalence is increasing among women of reproductive age. This has evident consequences for public health, as obesity is associated with several chronic diseases and premature mortality [1, 2]. In addition, obesity is associated with an increased risk of subfertility [3]. Women who have a body mass index (BMI, in kg/m^2^) above 24 have a significantly elevated relative risk of subfertility compared to women with lower BMIs [4]. Although the exact mechanism through which fertility is affected by body mass and body fat is uncertain, adipose tissue has been shown to disturb the secretion and bioavailability of sex hormones and to affect egg quality, via effects of insulin, leptin, and adipokines [5, 6]. In addition to obesity alone, polycystic ovary syndrome (PCOS) is a common endocrine disorder affecting 6–20 % of women of reproductive age [7] and is currently recognized as the leading cause of anovulatory infertility.

The mechanisms underlying the intrinsic insulin resistance in PCOS remain unclear, but potentially they are associated with increased abdominal visceral fat [8]. In other insulin resistant populations, exercise training has consistently been shown to improve cardiovascular risk factors and reduce the risk of type 2 diabetes [9–11]. Furthermore, insulin sensitivity has been found to increase after a period of exercise training [10, 12]. Sim et al. [13] found significantly improved pregnancy rates after a 12-week weight loss program including exercise advice and diet intervention in obese women undergoing assisted fertilization. A recent observational study [14] also indicated that regular physical activity is associated with improved fertility in obese women going through fresh in vitro fertilization (IVF) or intracytoplasmic sperm injection (ICSI) cycles. Still, there is a considerable gap in the research literature regarding the effects of exercise training on fertility outcomes, and future research should focus on well-designed, adequately powered studies to address this gap [15]. In particular, research is needed on the isolated effects of exercise training, i.e., in the absence of dietary interventions. Also, there is a great need to understand the potential mechanisms through which exercise training can affect fertility.

In this article, we describe the design and methods of the FertilEX trial, a randomized controlled trial of exercise training prior to assisted fertilization in overweight and obese women.

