### Randomization and allocation

Participants are stratified for PCOS (yes/no) and randomly assigned to either the intervention or control group after initial assessments in a 1:1 manner, as outlined in the flow diagram (Fig. 1). Randomization is performed by a web-based randomization system developed and administered by the Unit of Applied Clinical Research, Institute of Cancer Research and Molecular Medicine, NTNU, Trondheim, Norway. The randomization is in blocks with varying block size.

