### Power calculation and statistical analyses

A clinical pregnancy rate of 0.30 during the first treatment cycle can be expected in this patient group. As the research hypothesis of this study is original, we have little previous data to support the power calculation. Based on a previous pilot study on giving advice about exercise and diet to improve pregnancy rates [24], we expect that the pregnancy rate in the intervention group will be increased to 0.55. With a statistical power of 0.80 and a significance level of 0.05, it is estimated that 61 patients are needed in each group to demonstrate the increased pregnancy rate. To allow for an expected 15 % dropout, we will include 140 participants in the study. We will analyze the data using the intention-to-treat principle (main analysis). Since dropout is one of the main concerns in studies of lifestyle modifications, we will also analyze the data with a per protocol analysis, excluding women in the intervention group who did not follow the prescribed intervention (defined as attending less than 80 % of the exercise sessions). As women in the control group might start exercising on their own, in the per protocol analyses we will exclude women in that group reporting to do high-intensity endurance training (making them breathe heavily) twice weekly or more during the intervention period. The proportion of women with ongoing pregnancy in the intervention and control groups will be compared using stratified (for PCOS/not PCOS) analysis of 2 × 2 tables. Missing data regarding pregnancy and fertilization outcome will be imputed with a negative result or zero; i.e., if no oocytes are collected during the assisted fertilization, the fertilization rate will be regarded as missing. The null hypothesis is that the proportion is equal in both groups, while the alternative hypothesis is that the proportion is larger in the intervention group. Secondary outcomes will be analyzed using analysis of covariance (ANCOVA), as suggested by Vickers and Altman [25]. We will use intervention group (exercise/control) as a fixed factor in the analyses and the baseline value of each outcome measure and PCOS status (PCOS/not PCOS) as covariates. When data on secondary outcomes are missing, we will use multiple imputation if we can assume that the data are missing at random. If we assume that the data are not missing at random, we will analyze only available data.

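### Since February 2016 only the exercise arm defers treatment by 10 weeks, so for about 89% of the planned sample a difference cannot be attributed to HIT rather than deferral, as the stated hypothesis and conclusion still do

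*Protocol article*

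**What the plan says.** All places are in the Protocol article.

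- **The change** (Trial status and change in study protocol after trial initiation). From 16 February 2016, "from this time point on, the women allocated to the control group no longer wait for 10 weeks before the assisted fertilization treatment starts". The reason given is that women declined to join because of the delay. The same section says that "As of March 2016, we have included 16 women in the study", that controls lose their 10-week assessment, and that a second clinic began recruiting in February 2016.
- **The exercise arm** (Intervention). Training for 10 weeks still comes before fertility treatment. Nothing in the change section alters this.
- **The claim.** Objectives names HIT before IVF or ICSI as what will raise the pregnancy rate. The main Discussion does the same, and the Discussion paragraph of the Abstract says the trial will inform on the "effects of high-intensity exercise before assisted fertilization in subfertile overweight/obese women". None of these mentions deferral.
- **The analysis** (Power calculation and statistical analyses). "The proportion of women with ongoing pregnancy in the intervention and control groups will be compared using stratified (for PCOS/not PCOS) analysis". There is one control group, and PCOS is the only stratifying factor.

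**The concern.** Before the change, both arms waited 10 weeks and the randomised difference was the training programme. After it, two things differ between the arms: the programme, and a 10-week postponement of treatment that only the exercise arm has. The trial then answers a different question for women who joined later, but the article carries the same hypothesis and conclusion across both periods.

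What is at stake is the meaning of the result. A higher pregnancy rate in the exercise arm could come from HIT, from the interval, or from both. A null result could be a benefit of HIT offset by a cost of waiting. The Abstract proposes that beneficial programmes be considered for regular fertility care, so readers need to know which contrast was tested. The secondary outcomes cannot settle it: the change also removes the controls' 10-week measurements, and with them the between-arm comparison on which Objectives relies for a mechanism.

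**Working it through.** **Inputs from the article**

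- Planned total 140 ("To allow for an expected 15 % dropout, we will include 140 participants in the study") and allocation "randomly assigned to either the intervention or control group after initial assessments in a 1:1 manner".
- 16 women included by March 2016. Since the change came in February, 16 is an upper bound on those randomised under the matched wait.
- Control rate 0.30 ("A clinical pregnancy rate of 0.30 during the first treatment cycle can be expected in this patient group"), exercise-arm rate 0.55, power 0.80, significance level 0.05, 61 per group.

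**Step 1: the plan's own figure**

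Two proportions, two-sided, pooled variance, no continuity correction:

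n = [1.960 × √(2 × 0.425 × 0.575) + 0.842 × √(0.30 × 0.70 + 0.55 × 0.45)]² / 0.25²

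= (1.370 + 0.569)² / 0.0625 ≈ 60.2, rounded up to **61 per group**.

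The stated figure reproduces. Then 122 × 1.15 = 140.3, which gives the planned 140. Neither figure is in question here.

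**Step 2: share of the sample under each comparator**

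- Matched wait: at most 16/140 = 11.4%, or about 8 of 70 controls if the 16 split evenly.
- No added wait for controls: at least 124/140 = **88.6%**, or about 62 of 70 controls.
- If only 122 women are evaluable, the share is at least 106/122 = 86.9%.

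**Step 3: what a deferral effect would do (assumption)**

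Suppose deferral shifts the first-cycle pregnancy rate by d in every woman who defers, and 8 of 70 controls deferred.

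- Exercise arm with no exercise effect: 0.30 + d.
- Pooled control arm: 0.30 + (8/70)d.
- Expected contrast: d × 62/70 = 0.886d.

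The last column adds the planned 25-point exercise effect and gives two-sided power at 61 per group. With d = 0 it is 81%.

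| d (points) | Contrast with no exercise effect (points) | Power with the planned exercise effect |
|---|---|---|
| −10 | −8.9 | 45% |
| −5 | −4.4 | 64% |
| +5 | +4.4 | 91% |
| +10 | +8.9 | 97% |

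The values of d only show the range. The article supports none of them in particular.

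**Step 4: one route through the plan's own rules**

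Missing pregnancy outcomes count as negative. A woman who leaves during the 10 weeks is then a failure in the exercise arm, while controls randomised after the change have no matching pre-treatment period. As an extreme assumption, if the planned 15% dropout fell only there, a true 0.55 would be observed as 0.55 × 0.85 = 0.4675. Two-sided power against 0.30 at 70 per arm would then be about 53%.

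**The case against.** The strongest reply is that the comparator was always usual care. The Abstract and the aim at the end of Background describe the control condition as standard assisted fertilization only, and a woman who starts without an added wait fits that at least as well as one who waits. The 10-week lead-in is part of the intervention as described. The change came early, is disclosed with date and reason, and randomisation is concurrent on both sides of it. The endpoint is the initial cycle, so lost calendar time does not itself count against the exercise arm.

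Most of this stands, and it rules out four stronger readings that a reader might infer:

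- **That the primary test is invalid.** It is not. Within each period women are randomised to concurrent arms, so the intention-to-treat comparison is sound for the combined strategy.
- **That the article promises an effect of exercise separated from everything else.** Background does say that "research is needed on the isolated effects of exercise training, i.e., in the absence of dietary interventions", but the term is explained there as meaning without diet. It says nothing of timing.
- **That the change created the difference in contact with staff.** Supervised sessions and intensity checks belong to the intervention and are not described for waiting controls either. Only the difference in timing is new.
- **That a period stratum is needed in the primary analysis.** At most 16 women over two arms and two PCOS levels average 4 per cell. The stratified result would still be one estimate over both comparators, and period is confounded with the second clinic.

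It is also fair that an analysis by protocol version may sit in an analysis plan that is not shown, so its absence here is not the fault. What the reply does not answer is that Objectives and both Discussion texts still name HIT as the cause, although the published design no longer separates HIT from deferral for nearly all women.

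**Conclusion.** The point holds as one of attribution and labelling. For at least 88.6% of the planned sample the randomised contrast is HIT during a 10-week deferral, then treatment, against usual care without the added wait. The pooled comparison mixes this with a matched-wait contrast in at most 11.4%, and the article does not say so.

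This rests on two readings: that all 16 women included by March 2016 are counted as matched-wait, which makes 88.6% a minimum, and that recruitment reaches 140. The size and direction of any deferral effect are unknown from the documents, so no actual bias can be quoted. The shifts of about 4 to 9 points are illustrations under assumed effects of 5 to 10 points. The sample size calculation and the type I error of the primary test are not affected. It should be corrected before results are known, because it determines what the trial may conclude.

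**What to change.** 1. Restate the primary hypothesis and conclusion (Abstract Discussion, aim at the end of Background, Objectives, main Discussion) as the effect of a strategy: HIT during a 10-week deferral before treatment, versus usual care without the added wait. State that an effect of exercise cannot be separated from that of deferral.
2. Keep the PCOS-stratified primary analysis in all randomised women, and say that the control group contains two regimens.
3. Pre-specify a sensitivity analysis restricted to women randomised from 16 February 2016, using the same method.
4. Report the women randomised earlier descriptively, as the only matched-wait comparison, and note that the second clinic joined in the same month, so differences between periods cannot be assigned to the comparator.

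The cost is rewording, one variable derived from the randomisation date and one further analysis. The price is a narrower claim. At most 16 early women cannot estimate an exercise-only effect, and the sensitivity analysis will probably differ little from the main one. Its use is to give a result for a single, clearly named contrast.

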## Abstract

**Background:**

Overweight and obese women show reduced conception rates compared to women of normal weight. Insulin resistance and increased amount of visceral fat may be important mechanisms for reduced fertility in these women. Exercise training, in particular with high intensity, has previously been found to improve insulin sensitivity in overweight subjects. This study will assess if regular high-intensity interval training will improve the pregnancy rate after assisted fertilization compared to usual care only in overweight and obese women. We hypothesize that the intervention will improve pregnancy rate and insulin sensitivity compared to the control group.

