### Study assessment visits

Participants come for research visits at baseline and after the intervention period (10 weeks) (Fig. 1). Clinical data collected by the hospital recordings during the treatment will be available for the study investigators.

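### Since 16 February 2016 controls have no 10-week assessment, yet the article still plans a between-group ANCOVA of the 10-week secondary outcomes, and neither branch of its missing-data rule can supply the comparison

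*Protocol article*

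**What the plan says.** All references are to the protocol article.

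- **Trial status and change in study protocol after trial initiation:** "We made a change to the study protocol on 16 February 2016". From then on controls go straight to fertility treatment. The stated consequence is "This study change therefore implies there will be no assessments after 10 weeks for the women in the control group". On recruitment: "As of March 2016, we have included 16 women in the study". A second fertility centre was added in the same month.
- **Study assessment visits:** "Participants come for research visits at baseline and after the intervention period (10 weeks"), with no exception for controls.
- **Blinding:** post-intervention assessments are described without saying that they now apply to one arm only.
- **Power calculation and statistical analyses:** "Secondary outcomes will be analyzed using analysis of covariance (ANCOVA"), with exercise/control as the fixed factor and the baseline value and PCOS status as covariates. For missing secondary data, "we will use multiple imputation if we can assume that the data are missing at random". Otherwise only available data are analysed.
- **Abstract, Background:** "We hypothesize that the intervention will improve pregnancy rate and insulin sensitivity compared to the control group".
- **Outcome measures:** the secondary outcomes include insulin sensitivity, hormones, peak oxygen uptake, endothelial function, body weight and composition, quality of life, activity and diet. The fertility unit separately records eggs retrieved, fertilisation and embryo quality.

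**The concern.** An ANCOVA of a 10-week value by randomised group needs that value in both groups. Under the design now in force, controls randomised after the change will never have one. The article states what the change does to the assessments but does not carry it into the visit schedule, the secondary analysis or the abstract's hypothesis.

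At stake is the between-group evidence on insulin sensitivity, the first secondary outcome listed, and on the other outcomes measured at the research visit. If the analysis is run as written, the group effect rests either on an imputation model or on a handful of early controls. Nothing in the article would tell the analyst to label it as anything other than a randomised comparison.

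**Working it through.** **1. The plan's own figure.** The stated sample size is 61 per group for pregnancy rates of 0.30 and 0.55, power 0.80, significance level 0.05. With a two-sided test and pooled variance, the mean rate is 0.425 and

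n = [1.96 × √(2 × 0.425 × 0.575) + 0.842 × √(0.30 × 0.70 + 0.55 × 0.45)]² / 0.25² = 60.2, rounded up to 61.

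The figure reproduces. It concerns pregnancy only; the article gives no power figure and no SD for any secondary outcome.

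**2. Controls who can have a 10-week value.**
- Planned total: "To allow for an expected 15 % dropout, we will include 140 participants in the study". At 1:1 that is 70 per arm.
- Enrolled by March 2016: 16. The arm split is not given. Assuming 1:1, 16 / 2 = 8 controls.
- Share of the control arm: 8 / 70 = 11%. Without a value by design: (70 − 8) / 70 = 89%.
- Illustrative range, because the split, the number enrolled after 16 February and the number who completed 10 weeks are all unknown: 4 / 70 = 6% to 12 / 70 = 17%.

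**3. Branch A of the missing-data rule: missing at random is assumed, so multiple imputation.** Missingness is determined by arm and enrolment date, both observed, so this assumption could be argued and the branch could be taken. About 62 of 70 control values would then be imputed. If the imputation model contains arm, the control values are generated from about 8 early women. If it omits arm, they are borrowed from exercisers. Either way almost no information about untreated women is added.

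**4. Branch B: available data only.** This compares up to 70 exercisers with about 8 controls. If about 8 exercisers were also enrolled early, about 62 of the 70 came after the change, some possibly from the second centre, so most of the comparison is not concurrent.

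**5. Size of the loss.** The standard error of the difference, in SD units, is √(1/n₁ + 1/n₂):
- 61 v 61: √(2/61) = 0.181
- 70 v 8: √(1/70 + 1/8) = 0.373, which is 2.06 times larger

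Difference detectable with 80% power (two-sided 0.05, noncentral t, in units of residual SD):

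| Exercise v control | Detectable difference | Power for 0.5 SD |
|---|---|---|
| 61 v 61 | 0.51 SD | 0.78 |
| 70 v 12 | 0.89 SD | 0.35 |
| 70 v 8 | 1.06 SD | 0.26 |
| 70 v 4 | 1.46 SD | 0.16 |
| 8 v 8 (concurrent only) | 1.51 SD | 0.15 |

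Two degrees of freedom for the baseline and PCOS covariates leave the first four detectable differences unchanged to two decimals; 8 v 8 becomes 1.53 SD.

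**The case against.** **The imputation rule is conditional.** A reader might infer that the plan commits to imputing the control arm. It does not: the article also provides for available data only and specifies no imputation model. That is correct, and it is why both branches are worked through above. The second branch avoids invented values but leaves about 8 controls.

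**Eight is not a ceiling.** Randomisation is stratified with varying block sizes, and the count of 16 dates from after the change. This stands, hence the range of 4 to 12. The conclusion is the same throughout it.

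**The SD figures are illustrative.** This also stands. The article sets no target for secondary outcomes, so 0.51 SD is a benchmark for what 61 per group would have given, not a promise that the plan breaks.

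**The mechanism aim survives in part.** A reader might infer that it fails altogether. The documents do not support that. Egg quality is among the mechanisms named in the Background, and the egg, fertilisation and embryo data come from clinic records in both arms. The Objectives section words its insulin-sensitivity expectation within the exercise group, so it does not conflict with the change; the comparison with controls is in the abstract.

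**The primary outcome is untouched by the missing visit.** True: it is ascertained by ultrasound in routine care, and its sample size does not depend on the 10-week assessment.

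**The authors disclose the loss, and a separate analysis plan may deal with it.** They do disclose it. But the article itself fixes the secondary analysis and a missing-data rule, and that stated method conflicts with the stated design.

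**Conclusion.** The point holds for secondary outcomes that need the 10-week research visit, and for those only. The visit schedule, the blinding section, the secondary analysis and the abstract's insulin-sensitivity hypothesis are not reconciled with the change of 16 February 2016. About 8 of 70 controls can contribute a 10-week value, so about 89% are absent by design. Neither imputation nor available-data analysis restores the comparison, and the detectable difference roughly doubles, from 0.51 SD to about 1.06 SD (0.89 to 1.46).

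This rests on three assumptions: the first 16 women split roughly evenly (range shown), the remaining controls are recruited under the changed design, and effects are expressed in residual SDs because the article gives none. The evidence does not show that the primary analysis, or the whole mechanistic aim, is lost through the missing visit.

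**What to change.** 1. Reconcile Study assessment visits, Blinding, Power calculation and statistical analyses, and the abstract's Background with the section on the change in protocol.
2. Restrict the between-group ANCOVA of 10-week outcomes to women randomised before the change, and label it exploratory.
3. For women randomised later, report the exercise-arm change from baseline with a 95% CI, described as uncontrolled, without a between-group p-value.
4. State that multiple imputation is not applied to control values that were never scheduled.
5. Keep the abstract's insulin-sensitivity hypothesis on record and state that its between-group form can no longer be adequately tested.
6. Keep randomised comparisons for eggs retrieved, fertilisation and embryo quality.

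The cost is wording, and it is low while only 16 of 140 women are enrolled. The restricted ANCOVA will detect only very large differences (about 1.5 SD at 8 v 8), so the mechanistic claim becomes weaker. The change of February 2016 has already caused that; the revision only makes it visible.
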